### Sample size calculation

We calculated the sample size based on the rate of early initiation of breastfeeding, which is one of the primary outcomes in this study. According to our pilot investigation and previous literature [4, 20], the rate of early initiation of breastfeeding is 40% in the control group (receiving routine care), and the rates in the intervention group 1 (receiving EENC with SSC for 30 min), intervention group 2 (receiving EENC with SSC for 60 min), and intervention group 3 (receiving EENC with SSC for 90 min) are supposed to be 60%, 70%, and 80%, respectively. Accounting for multiple comparisons (SSC for 30 min vs. routine care, SSC for 60 min vs. routine care, SSC for 90 min vs. routine care, SSC for 30 min vs. SSC for 60 min, SSC for 30 min vs. SSC for 90 min, SSC for 60 min vs. SSC for 90 min), a level of significance is set to be 0.008 (0.05/6) by using Bonferroni adjustments. For 80% power, the sample size required for each of the control group and the intervention group 1 is 152 participants; the sample size required for each of the control group and the intervention group 2 is 64 participants; the sample size required for each of the control group and the intervention group 3 is 34 participants. The largest sample size group (*n*=152) is selected as the number of recruitment in each group. Considering 15% of loss to follow-up, the number of participants in each group is finally set to be 180 and adds up to a total of 720 participants. One hundred eighty participants will need to be recruited in each of four hospitals, which means that each of the hospital will recruit 45 participants in the control group, intervention group 1, intervention group 2, and intervention group 3, respectively. The sample size calculation was performed using PASS 2011 software (NCSS, Kaysville, UT, USA).

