## Discussion

In China, EENC during vaginal deliveries has been performing since 2016 and contributed to increased rates of exclusive breastfeeding and improved maternal and neonatal health [4, 6, 15], while the evidence during cesarean deliveries remains lacking. The objective of this multi-centered randomized controlled study is to evaluate the effectiveness of EENC for cesarean section newborns on exclusive breastfeeding rates and early initiation of breastfeeding rates in China.

To the best of our knowledge, this study is the first multi-centered randomized controlled trial with relatively large sample size to determine the impact of EENC on improvement of breastfeeding outcomes and maternal and neonatal health for cesarean section newborns in China. We will recruit eligible women from four tertiary hospitals in four provinces that have been providing EENC during vaginal deliveries and accumulated abundant experience in EENC practices. All obstetricians, midwives, and researchers involved in implementation of EENC in four study sites were coached by national facilitators and passed post-coaching evaluations. Another strength of this study is that we will examine associations between the duration of SSC and breastfeeding performance, which will provide evidence-based recommendation to inform optimal duration of SSC for cesarean deliveries. The results of this study have potential to inform national-level guidelines and policy-making for optimizing EENC implementation for cesarean section newborns.

There are several limitations in this study. First, we currently focus on healthy mother and newborn pairs. Further studies will be needed among low-risk and high-risk mothers and newborns. Second, all study sites are tertiary-level hospitals with specialized obstetricians and midwives and advanced medical devices to ensure safety of mothers and newborns. In future studies, we plan to extend EENC implementation for cesarean section newborns to all levels of hospitals.

In conclusion, this is the first multi-centered randomized controlled study in China to assess the impact of EENC on improvement of breastfeeding outcomes and explore the optimal duration of SSC among newborns born by cesarean section. Our findings will enable making evidence-informed guidelines and policies.

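### The sample size covers only three of the six named comparisons: on the plan's own rates, 30 vs 60 min and 60 vs 90 min have about 20% and 26% power at 152 per arm

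*Protocol article*

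**What the plan says.** All of the sizing is in one paragraph of the protocol article, under Sample size calculation.

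- **Endpoint:** "We calculated the sample size based on the rate of early initiation of breastfeeding", one of two primary outcomes.
- **Rates:** 40% under routine care; the rates with 30, 60 and 90 min of skin-to-skin contact (SSC) "are supposed to be 60%, 70%, and 80%, respectively".
- **Comparisons:** each duration against routine care, plus all three pairs of durations. The list includes "SSC for 30 min vs. SSC for 60 min, SSC for 30 min vs. SSC for 90 min", and then 60 vs 90 min.
- **Alpha:** "a level of significance is set to be 0.008 (0.05/6) by using Bonferroni adjustments".
- **Requirement:** "For 80% power, the sample size required for each of the control group and the intervention group 1 is 152 participants". The other two control comparisons are given 64 and 34. The largest figure, 152, "is selected as the number of recruitment in each group", and 15% loss takes it to 180 per arm and 720 in total.

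No sample size or power is given for any comparison between durations. Yet the Discussion names as a strength that the trial will give an "evidence-based recommendation to inform optimal duration of SSC for cesarean deliveries", and the Abstract's Discussion paragraph promises much the same.

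**The concern.** Dividing alpha by six makes all six comparisons part of the confirmatory family. The arm size was then chosen as the largest of three requirements, all from contrasts of 20 to 40 percentage points against control. The steps between neighbouring durations are only 10 points on the plan's own rates, so they need far more participants than any contrast that was sized.

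The adjacent comparisons matter because they show whether 60 min improves on 30, and whether 90 improves on 60. If the plan's dose-response is exactly true, a non-significant result is still the most likely outcome for each of them. A reader who knows that the arms were sized at 80% power, and who sees no power for these pairs, could take that result as support for shorter contact. The article says that its results may inform national guidelines.

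**Working it through.** **Inputs.** Rates 0.40, 0.60, 0.70, 0.80; alpha 0.008 per comparison; power 80%; 15% loss (all from Sample size calculation). Allocation 1:1:1:1 (Study design). Two-sided testing (Analysis plan). The normal quantiles are z(0.996) = 2.652 and z(0.80) = 0.842.

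**Formula** (two proportions, pooled variance under the null, no continuity correction, equal arms), with m the mean of p1 and p2:

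n per arm = [2.652·√(2m(1−m)) + 0.842·√(p1(1−p1) + p2(1−p2))]² / (p1 − p2)²

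**Step 1: reproduce the plan's figure.** For 40% vs 60%: (2.652·√0.50 + 0.842·√0.48)² / 0.04 = 151.1, so 152. This matches exactly. The other control comparisons give 66 (stated 64) and 36 (stated 34), each within two participants. Loss: 152/0.85 = 178.8, so 179 (stated 180).

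**Step 2: apply the same formula to the three pairs not sized.**

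- 30 vs 60 min (60% vs 70%): (2.652·√0.455 + 0.842·√0.45)² / 0.01 = 553.9, so **554**
- 60 vs 90 min (70% vs 80%): (2.652·√0.375 + 0.842·√0.37)² / 0.01 = 456.2, so **457**
- 30 vs 90 min (60% vs 80%): (2.652·√0.42 + 0.842·√0.40)² / 0.04 = 126.7, so **127**

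The adjacent pairs need 554/152 = 3.6 and 457/152 = 3.0 times the chosen arm size. With 15% loss they become 554/0.85 = 652 and 457/0.85 = 538 per arm.

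**Step 3: power at the planned size.** Power = Φ{[|p1 − p2|·√n − 2.652·√(2m(1−m))] / √(p1(1−p1) + p2(1−p2))}. For 30 vs 60 min at n = 152 this is Φ{(1.233 − 1.789)/0.671} = Φ(−0.829) = 0.204.

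| Comparison | 152 per arm | 180 per arm (no loss) |
|---|---|---|
| 30 vs 60 min | 20.4% | 25.2% |
| 60 vs 90 min | 26.0% | 32.1% |
| 30 vs 90 min | 88.1% | 93.6% |
| Control vs 30 min | 80.3% | 87.8% |

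Exact binomial enumeration of the same test gives 20.3%, 26.0% and 88.4% at 152 for the three duration pairs, and 25.2%, 32.3% and 93.9% at 180.

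**Step 4: sensitivity.** Requirements for 30 vs 60 and 60 vs 90 min:

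- alpha 0.05/6 unrounded: 550 and 453
- unpooled variance: 550 and 452
- continuity correction: 574 and 477
- one-sided 0.008: 480 and 395

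At an unadjusted two-sided 0.05, power is 44.7% and 52.1% at 152, and 51.2% and 59.2% at 180. No variant brings either pair near 80%.

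**Step 5: precision.** At 152 per arm, the half-width of a 99.2% interval for 30 vs 60 min is 2.652·√(0.45/152) = 14.4 points. For 60 vs 90 min it is 2.652·√(0.37/152) = 13.1 points. Both exceed the assumed 10-point difference.

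**The case against.** **The plan does not claim 80% power for these pairs.** A reader might infer that the protocol states 80% power for all six comparisons and is therefore false. The text does not support that: it attaches 80% pair by pair, and only to the control comparisons. Nor is 152 miscalculated, and it is the largest of the three figures listed. This objection stands. The defect is that two members of the declared family were left unsized and their power undisclosed.

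**The main purpose is adequately sized.** The Background gives the purpose as comparison with routine care, and those comparisons reach about 80% or more. The 30 vs 90 min contrast is covered too. So the trial is not underpowered overall. But the Study design section compares all four groups, and the Abstract and Discussion promise guidance on duration, so the gap falls on a stated aim.

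**20% and 26% are the lower case.** They assume the full 15% loss. Early initiation is observed within an hour of birth, and the Analysis plan specifies intention-to-treat with multiple imputation, so 25% and 32% may be nearer. Both sets should be shown; neither approaches 80%.

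**Nothing in the article claims equivalence.** This is true, and the trial is described as a superiority trial. The misreading is a foreseeable risk, not something the plan asserts.

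**A trend test might seem to rescue the duration question.** It does not. With three equal, equally spaced arms its weights are −1, 0 and +1, so its numerator is the 90 min rate minus the 30 min rate. In simulation at 60/70/80% with 152 per arm and alpha 0.008, its power was 0.882 against 0.883 for the plain 30 vs 90 min test, with the same decision in 99.4% of runs. It cannot separate 60 min from 30 or 90. Its power rests on early-initiation rates and does not carry over to exclusive breastfeeding, for which the article gives no rates by duration.

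**Conclusion.** The point holds in a limited form. On the plan's own rates and alpha, 152 per arm supports four of the six named comparisons: the three with routine care, and 30 vs 90 min. It does not support 30 vs 60 or 60 vs 90 min, which need 554 and 457 per arm. Their power is about 20% and 26% at 152 evaluable per arm, or 25% and 32% at 180. If the assumed 10-point steps are real, those tests would miss them about 80% and 74% of the time at 152.

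The result takes the assumed 60%, 70% and 80% at face value. The 70% vs 80% gap may be generous. Early initiation means a first breastfeed completed within an hour of birth, and the 60 and 90 min arms are both assigned contact for that whole hour. A smaller true gap would lower the power further.

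The trial can test whether 90 min differs from 30 min. It cannot be expected to show where between them the benefit lies.

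**What to change.** Amend the text as follows; no extra participants are needed.

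1. In Sample size calculation, describe 152 as the largest requirement among the three control comparisons. State that 80% power applies to those three and to 30 vs 90 min (127 needed, about 88% at 152), and not to the adjacent durations.
2. Give the power for 30 vs 60 and 60 vs 90 min: about 20% and 26% at 152 evaluable per arm, and 25% and 32% at 180.
3. In the Analysis plan, say that these two comparisons will be reported as estimated differences with confidence intervals.
4. State that a non-significant difference between adjacent durations is not evidence that the shorter one is as good. Limit the optimal-duration statements in the Abstract and Discussion accordingly.

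Do not substitute a trend test for the adjacent comparisons, because it would largely repeat 30 vs 90 min.

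The cost is a less favourable stated power for the duration comparisons and a more modest claim about optimal duration.

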### Analysis plan

Baseline characteristics of participants will be presented as mean (standard deviation) for continuous variables and number (percentage) for categorical variables. Data will be analyzed on an intention-to-treat basis to compare primary and secondary outcomes in four groups. The chi-square test or one-way analysis of variance will be used to compare the characteristics and rates of exclusive breastfeeding and early initiation of breastfeeding, and maternal and neonatal outcomes among the 4 groups (control group, intervention group 1, intervention group 2, and intervention group 3). For missing data, we will use multiple imputation to obtain complete datasets. All the statistical analyses will be conducted using SPSS 20.0 statistical software (SPSS Inc., Chicago, Illinois). A two-sided *P* value <0.05 indicated significance.

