### Randomization and blinding

The randomization sequences are generated by the biostatistician using the random number sequence generator function in SAS software version 9.2 (SAS Institute, Cary, NC), with stratification by study sites. Participants will be assigned a randomization code according to their sequential numbers and randomly allocated into one of four groups with a 1:1:1:1 ratio in the operating room. Due to the nature of EENC interventions, blinding of participants, obstetricians, nurses/midwives, and intraoperative research staff is infeasible.

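### Randomisation is stratified by hospital but the planned tests ignore hospital: a conservative and less efficient analysis if hospitals differ, and nearly free to correct

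*Protocol article*

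**What the plan says.** Three sections of the protocol article bear on this.

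- **Randomization and blinding:** the sequence is generated "with stratification by study sites", and participants are "randomly allocated into one of four groups with a 1:1:1:1 ratio in the operating room". No blocks are mentioned.
- **Sample size calculation:** "each of the hospital will recruit 45 participants in the control group, intervention group 1, intervention group 2, and intervention group 3, respectively". The calculation takes 40% early initiation under routine care. The 30, 60 and 90 min arms "are supposed to be 60%, 70%, and 80%, respectively". It uses a Bonferroni level of 0.008 and 80% power.
- **Analysis plan:** "The chi-square test or one-way analysis of variance will be used to compare the characteristics and rates" of the primary outcomes, and the maternal and neonatal outcomes, among the four groups. No hospital factor, stratified test or regression model is named. The same paragraph says "For missing data, we will use multiple imputation to obtain complete datasets".

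**The concern.** When arms are balanced within each hospital, differences between hospitals cannot contribute to differences between arms. An unstratified chi-square test or one-way ANOVA still counts that variation as error. Its standard error is then larger than the design warrants, so the test rejects too rarely under the null and has less power than a test that respects the strata.

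The article does not leave this open. It names specific unstratified methods that do not match its own randomisation. Hospital differences are plausible, since the four sites are in four provinces, although no figures are given. At stake is efficiency, above all for comparisons between durations of skin-to-skin contact, where the assumed differences are smallest and the article hopes to recommend an optimal duration.

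**Working it through.** **1. The plan's own figure.** Inputs from Sample size calculation: 40% vs 60%, two-sided 0.008, 80% power. With the pooled-variance formula,

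n = [z(0.996)·√(2·0.5·0.5) + z(0.80)·√(0.4·0.6 + 0.6·0.4)]² / 0.2² = [2.652·0.7071 + 0.842·0.6928]² / 0.04 = 151.1, so 152 per arm.

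152/0.85 = 178.8, which the article sets at 180. The figure reproduces, and no hospital term is needed to reach it.

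**2. Assumed hospital rates.** The article gives none, so I took three sets of control rates, each averaging 40%: (a) 40% everywhere; (b) 20/35/45/60%; (c) 10/30/50/70%. The comparison arm has a common odds ratio chosen to average 60%: 2.25, 2.44 and 2.85 respectively.

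**3. Type I error by hand.** The unstratified test uses variance p̄(1−p̄) = 0.4·0.6 = 0.24. With balance within hospital, the true variance is the mean of p_h(1−p_h).

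- (b) (0.16 + 0.2275 + 0.2475 + 0.24)/4 = 0.21875. The ratio to 0.24 is 0.911, with square root 0.955. The effective critical value is 1.96/0.955 = 2.05, so type I error is about 4.0%.
- (c) (0.09 + 0.21 + 0.25 + 0.21)/4 = 0.19. The ratio is 0.792, with square root 0.890. The effective critical value is 1.96/0.890 = 2.20, so type I error is about 2.8%.

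**4. Simulation.** 400,000 two-arm trials per scenario, with 38 per arm per hospital (152 in total) or 45 (180 in total). The unstratified chi-square is compared with the Cochran-Mantel-Haenszel (CMH) test by hospital, whose statistic is z = Σ(x₁h − t_h/2) / √Σ[m²·t_h(2m − t_h)/((2m)²(2m − 1))], where m is the number per arm per hospital, x₁h the events in one arm and t_h the events in both arms. Each cell gives chi-square / CMH.

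| Rates | Per arm per hospital | Type I error at 5% | Power at 0.05/6 | Power at 0.008 |
|---|---|---|---|---|
| (a) | 38 | 5.3% / 5.2% | 82.3% / 80.4% | 79.3% / 79.5% |
| (a) | 45 | 4.9% / 4.8% | 87.9% / 87.7% | 87.1% / 87.2% |
| (b) | 38 | 4.2% / 5.0% | 83.5% / 85.1% | 80.4% / 84.7% |
| (b) | 45 | 3.9% / 5.0% | 88.9% / 91.3% | 88.2% / 91.1% |
| (c) | 38 | 2.9% / 5.0% | 85.3% / 90.9% | 82.1% / 90.7% |
| (c) | 45 | 2.6% / 4.9% | 90.5% / 95.4% | 89.9% / 95.3% |

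In (b) and (c) the shortfall is about 2 to 6 points at 0.05/6. At the rounded level 0.008 with 38 per arm per hospital it is 4 to 9 points. The two levels are almost the same. The jump between them at 152 per arm arises because the unstratified statistic takes few distinct values near the cut-off, which is also why (a) shows 82.3% and 79.3%.

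**5. Other tests and contrasts.** These use 45 per arm per hospital and hospital log-odds with SD 0.5 (control rates about 25–56%) or 1.0 (about 14–70%).

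- Four-group chi-square at 5%: type I error 4.1% and 2.2%, against about 5% when stratified.
- 60% vs 70% at 0.05/6: power 0.25 vs 0.28 and 0.24 vs 0.33 (unstratified vs stratified), against 0.26 for both with no spread.
- One-way ANOVA with 5, 10 or 20% of variance between hospitals: type I error 4.2%, 3.2% and 2.1%. With a hospital term it stays near 5%.

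**6. Dependence on balance.** With simple randomisation within hospital, the unstratified type I error was 5.2% and 5.1% at the same two spreads, so the conservatism disappears.

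**The case against.** The strongest reply is that nothing the trial planned for is lost. Unstratified power for 40% vs 60% does not fall as hospitals spread apart. It stays between 79.3% and 90.5% across the table, and is at least 87% with all 180 per arm. For the four-group test on early initiation at 40/60/70/80%, power is essentially 1 with or without stratification. The 60% vs 70% contrast is weak under either test. The size rests on assumed spreads, 10–70% is an extreme one, and the Discussion points to some uniformity: all sites are tertiary, already practise this care for vaginal births, and had staff coached and evaluated. The conservatism also needs near-balance within hospital, and 45 per arm is a recruitment target with no blocks stated.

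All of this stands as a limit on size. It does not remove the mismatch between a stratified design and an unstratified analysis.

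A reader might also infer that the reported intervals will be too wide, or that the imputed analysis has no combined result. The article supports neither. It specifies no intervals. Group rates and their differences can be pooled over imputed datasets, and rules exist for combining chi-square and F statistics. Silence on pooling is ordinary in a condensed article and is not an error.

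**Conclusion.** The point holds as a modest efficiency point. If hospital rates differ and arms are near-balanced within hospital, the named tests are conservative and less powerful than hospital-stratified ones. The direction is sure under those two conditions; the size is assumed. For control rates from 20–60% to 10–70%, type I error is about 4.2% to 2.6% at nominal 5%, and power for 40% vs 60% at 0.05/6 is about 2 to 6 points lower. With no hospital differences there is essentially no loss.

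It would be wrong to conclude that the trial is underpowered for its planned control contrast or at risk of false positives from this source. The contrast stays near or above its 80% target, and the error is on the conservative side.

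**What to change.** Include hospital in the analysis of every outcome.

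- **Binary outcomes:** logistic regression with arm and hospital as fixed effects, or a CMH test stratified by hospital.
- **Continuous outcomes:** linear regression with arm and hospital in place of one-way ANOVA.
- **Reporting:** hospital-adjusted effects with confidence intervals. If risk differences are wanted from the logistic model, they need a further standardisation step, which should be stated.

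As a side benefit, these estimates and standard errors can be combined over the imputed datasets by Rubin's rules; hospital should then also be in the imputation model.

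The cost is a change of analysis wording, with no further participants or data. If hospitals turn out alike, almost nothing is given up: at 45 per arm per hospital, power at 0.05/6 is 87.9% unstratified and 87.7% stratified.

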**Methods:**

This is a multi-centered, randomized controlled trial conducted in 4 tertiary hospitals in China. A total of 720 eligible women who will receive cesarean section are being randomized into four groups: control group (*n*=180), intervention group 1 (skin-to-skin contact for 30 min, *n*=180), intervention group 2 (skin-to-skin contact for 60 min, *n*=180), and intervention group 3 (skin-to-skin contact for 90 min, *n*=180). The control group will receive routine care, whereas the intervention groups will receive EENC with different duration of skin-to-skin contact. Demographic characteristics, clinical information, and breastfeeding outcomes will be collected. The primary outcome is rates of exclusive breastfeeding and early initiation of breastfeeding, and the secondary outcomes include maternal and neonatal morbidity and admissions.

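### Baseline characteristics of randomised arms are to be significance-tested, and the only tests named for the two primary outcomes use neither study site nor any other baseline variable

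*Protocol article*

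**What the plan says.** The Analysis plan of the protocol article begins with a descriptive table: "Baseline characteristics of participants will be presented as mean (standard deviation) for continuous variables and number (percentage) for categorical variables". It then adds tests: "The chi-square test or one-way analysis of variance will be used to compare the characteristics and rates of exclusive breastfeeding", and the same sentence goes on to early initiation of breastfeeding and the maternal and neonatal outcomes, compared among the four groups. The section closes with "A two-sided *P* value <0.05 indicated significance". It names no covariate, no model and no stratified test.

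The section on randomisation and blinding says that the sequences are stratified by study site and that allocation is 1:1:1:1. On baseline data, the Abstract says only: "Demographic characteristics, clinical information, and breastfeeding outcomes will be collected". Parity and previous breastfeeding are not mentioned anywhere in the article.

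**The concern.** There are two linked points.

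1. **Tests of baseline characteristics.** If randomisation was carried out properly, any baseline difference between arms arose by chance. A P value then answers a question whose answer is already known. It does not say whether an imbalance matters, which depends on how strongly the variable predicts the outcome. A significant result may cast unwarranted doubt on the trial or prompt adjustment for whichever variable happened to differ. With no covariates named in advance, and in an open-label trial, that choice would be hard to defend.

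2. **Unadjusted primary comparisons.** Both primary outcomes are binary and compared by an ordinary chi-square test. This makes no use of site, although the design stratifies by it, or of any prognostic baseline variable. If such variables predict breastfeeding, some precision is given up.

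**Working it through.** **Reproducing the plan's own figure.** The Sample size calculation takes 40% in the control arm, and the three intervention rates "are supposed to be 60%, 70%, and 80%, respectively". It states that "a level of significance is set to be 0.008 (0.05/6) by using Bonferroni adjustments", and "For 80% power, the sample size required for each of the control group and the intervention group 1 is 152 participants". With the pooled-variance formula, two-sided and without continuity correction:

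n = [z(1−α/2)·√(2p̄(1−p̄)) + z(0.80)·√(p1(1−p1) + p2(1−p2))]² / (p2−p1)²

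For p1 = 0.40, p2 = 0.60, p̄ = 0.50 and α = 0.008: (2.652 × 0.7071 + 0.8416 × 0.6928)² / 0.04 = 6.04 / 0.04 = 151.1, so 152. At α = 0.05/6 it is 150. The other two comparisons give 66 and 36 at α = 0.008, against the stated 64 and 34. Allowing for loss, 152 / 0.85 = 179, against the stated 180. The plan's setting is therefore a fair base for what follows.

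**Chance findings at baseline.** For k independent characteristics tested at 0.05, the chance of at least one significant result is 1 − 0.95^k:

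- k = 5: 23%
- k = 10: 40%
- k = 15: 54%

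It passes one half only at k = 14 (51%; k = 13 gives 49%). The article does not say how many characteristics will be tested, and correlation between them would change these figures. As a check, a simulated chi-square test on a 50% characteristic in 4 × 180 women rejected in 4.6% of runs, as expected for a true null.

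**Possible gain from adjustment.** The article gives no prognostic strength for any baseline variable, so this part rests on an assumption: a binary covariate present in half the women that shifts the outcome rate by d in both arms. The variance it explains is R² = 0.25·d² / (0.4 × 0.6), that is 1.0%, 4.2%, 9.4% and 16.7% for d = 10, 20, 30 and 40 points. The equivalent increase in sample size is 1/(1−R²) − 1, or about 1%, 4%, 10% and 20%. Power for 40% versus 60% at two-sided 0.008, by simulation (40,000 runs per setting), Pearson test versus covariate-stratified Cochran-Mantel-Haenszel test:

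| Assumed covariate effect | 152 per arm | 180 per arm |
|---|---|---|
| 10 points | 0.794 vs 0.807 | 0.871 vs 0.880 |
| 20 points | 0.789 vs 0.820 | 0.873 vs 0.895 |
| 30 points | 0.793 vs 0.847 | 0.872 vs 0.913 |
| 40 points | 0.794 vs 0.884 | 0.874 vs 0.937 |

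The small gains are sensitive to the exact level because the unadjusted test is discrete. At 152 per arm and α = 0.05/6 the pairs are 0.819 vs 0.824, 0.821 vs 0.850 and 0.824 vs 0.887 for 20, 30 and 40 points, with a slight loss at 10 points or below.

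These figures cover one comparison on early initiation. The sample size section gives no rate for exclusive breastfeeding, so the effect on that outcome cannot be computed. No site-specific rates are given either, so the gain from accounting for site is not quantified.

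**The case against.** The case against is substantial, and most of it limits the point without removing it.

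- **Not adjusting is not an error.** An unadjusted chi-square test is valid under randomisation, and an article may leave adjusted analyses to a full analysis plan. This stands: the second point is an improvement, not the correction of a mistake. It does not protect the baseline tests, which the article states outright.
- **Parity and previous breastfeeding are not in the document.** A reader might infer that a known, free gain in power is being thrown away. The article does not support that: it neither names these variables as collected nor says how well they predict the outcome.
- **A spurious imbalance is not shown to be likely.** A reader might expect that one will probably be reported. That needs about 14 or more independent variables, and no count is given.
- **The baseline tests change no result.** The plan attaches no action to them, and deleting them alters no estimate, sample size or power figure. This also stands. The risk is of misreading and of unplanned adjustment.
- **152 per arm is the setting after full loss.** The plan recruits 180 per arm, and the outcomes are measured within an hour of birth and at discharge, so retention may be better than assumed. At 180 the unadjusted power is already about 0.87 to 0.88, and the gains are smaller.

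It could also be said that the characteristics tested need not be baseline ones. The opening sentence of the same section makes baseline the natural reading.

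**Conclusion.** The point holds as a minor one. The article commits to significance tests of characteristics between randomised arms, and these are uninformative; the chance of at least one spurious finding is about 23%, 40% or 54% for 5, 10 or 15 independent variables. It also names only unadjusted tests for both primary outcomes. Those tests are valid, but they leave out site, the one baseline factor that the design itself singles out, and any other prognostic information.

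The benefit of adjusting is conditional. At 152 per arm and α = 0.008 it runs from about nil to 1 point of power for a 10-point covariate effect, through about 3 and 5 points for 20 and 30, to about 9 points for 40. At 180 per arm the last three are about 2, 4 and 6 points. All of this assumes a covariate split evenly between the women and a strength that the documents do not supply. Nothing here suggests that the planned primary tests are invalid or biased.

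**What to change.** 1. In the Analysis plan, remove the characteristics from the sentence that lists the tests. The descriptive table promised at the start of the section is sufficient.
2. For both primary outcomes, pre-specify an analysis stratified by or adjusted for study site. If they are recorded among the clinical information collected, add parity or previous breastfeeding (yes/no). A Mantel-Haenszel analysis or logistic regression with standardised risk differences would serve.
3. State that covariates are fixed in advance and never chosen from baseline P values.
4. Keep the unadjusted comparison as a sensitivity analysis.

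The cost is a change of wording and one extra modelling step. Sample size and study conduct are unaffected. If neither parity nor previous breastfeeding is recorded, the site-stratified analysis can still be done.
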